##### Cost effectiveness

An economic evaluation will be performed using a questionnaire to assess direct health care costs as well as direct non-health related costs. The questionnaire is composed of 24 questions regarding costs of the last six months. The data will be used for a cost-effectiveness analysis, which will be done by the UMCG Medical Technology Assessment office.

### Statistical analyses

To estimate the effect of the interventions, analyses will be performed using SPSS 12.0 for the outcome measures. The baseline characteristics from both study groups will be compared for equality by means of an Independent Samples T-test (p-value 0.05) for continuous variables and a chi-square test for dichotomous variables. To compare treatment effects from measurement points T_0 _to T_4_, a GLM repeated measures analyses will be performed. Data will be analyzed according to the intention-to-treat principle and the per-protocol principle.

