### Study population

#### Sample size

The aim is to include 70 participants in the study. This number is based on the assumption that one year after randomization 50% of the participants will have recovered with conservative treatment [22,23] and 85% will successfully recover by means of arthroscopic subacromial decompression. The latter assumption is based on recovery rates presented in earlier studies in which successful results of arthroscopic subacromial decompression are reported in 86 to 95% of the cases [24-26]. A power analysis has been based on the effects of these treatments on shoulder function. In this study shoulder function will be measured with the Shoulder Disability Questionnaire, which is an outcome measure comparable to the instruments used in the referred articles. In order to detect a clinically relevant difference in shoulder function (35% differences in means) one year after randomization between the intervention and control group, 64 participants are needed – 32 in each group. These numbers are based on a power (1-B) of 0.80 and a significance level of 5% (two-sided). When a dropout rate of 10% is taken into account, 70 participants are to be included.

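### Baseline tests cannot show that the groups are equal, and the T0-to-T4 repeated measures model treats the pre-treatment scores as outcomes instead of adjusting for the score at randomization

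*Protocol article*

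**What the plan says.** Under Statistical analyses, the protocol article states that baseline characteristics of the two groups "will be compared for equality by means of an Independent Samples T-test (p-value 0.05) for continuous variables" and by "a chi-square test for dichotomous variables". It does not say what follows from either result.

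The same section compares treatment effects by GLM repeated measures over measurement points T0 to T4, under both intention-to-treat and per-protocol. It names no covariate, and it does not say whether the treatment contrast is the group effect or the group-by-time term.

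Under Outcome assessment, T0 is inclusion, T1 is randomization, and T2, T3 and T4 are three, six and 12 months later. So T0 and T1 both precede the randomized treatment. The physical assessment takes place only at T1 and T4.

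Under Sample size, "64 participants are needed – 32 in each group", raised to 70 for dropout. The groups are formed by randomization in blocks of four per general practitioner.

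**The concern.** There are two separate weaknesses.

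First, the t-test and the chi-square test look for a difference. They have no equality margin, so p > 0.05 is not evidence of equality. Because the groups are randomized, any baseline difference is due to chance and a significant result is a false alarm. What matters is how large an imbalance is and how strongly the variable predicts the outcome. The p-value measures neither.

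Second, the model puts the inclusion and randomization scores on the outcome side. The score at randomization is likely to be a strong predictor of the 12-month Shoulder Disability Questionnaire (SDQ) score, and it is already collected. Used as an outcome level, it either enters as a change score or is averaged into a group effect. Neither use is as good as adjusting for it. With about 64 evaluable participants, the precision lost and the sensitivity to a chance imbalance are both worth avoiding. The Discussion expects a positive result to lead to guideline revision, so a statement that the groups were comparable should not rest on p > 0.05.

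**Working it through.** **Inputs from the article.** 32 evaluable per arm (35 per arm at 70 randomized); baseline test threshold 0.05, taken as two-sided because the sidedness is not stated; visits T0 to T4.

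**Inputs not in the article (assumptions).** T1-to-T4 correlation r of the SDQ, shown at 0.3, 0.5 and 0.7, with equal SDs at both visits. The effect used for power is 0.711 SD, which an unadjusted comparison at T4 detects with 80% power at 32 per arm. It is a benchmark only, since the article gives no SD.

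**The plan's own figure.** For 50% against 85% recovery (two-sided 5%, power 0.80), the standard two-proportion formula gives 27 per arm without continuity correction and 33 with it (32.4 before rounding up). The stated 32 is close to the latter. For dropout, 64 × 1.1 = 70.4 against the stated 70. So 32 and 35 per arm are sound inputs here.

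**Step 1: largest observed baseline difference that passes.** d = t(0.975; 2n − 2) × √(2/n).
- n = 32: 1.999 × 0.250 = 0.50 SD
- n = 35: 1.995 × 0.239 = 0.48 SD
- Dichotomous variables, n = 32, uncorrected chi-square: 12/32 against 19/32 passes, a gap of 7/32 = 22 percentage points.

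**Step 2: how often chance produces such imbalances.** Under randomization the imbalance on one variable has standard error √(2/32) = 0.25 SD. It exceeds 0.25 SD in about 32% of trials and 0.50 SD in about 4.6%. So about 27% of trials have an imbalance between these values on a given variable, and the test flags none of them.

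**Step 3: expected shift with no treatment effect, given an imbalance d at T1.** Take d = 0.49 SD, just inside the threshold.

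| Contrast | Formula | r = 0.3 | r = 0.5 | r = 0.7 |
|---|---|---|---|---|
| T1-to-T4 change | (r − 1)d | −0.34 | −0.25 | −0.15 |
| T4 adjusted for T1 | 0 | 0 | 0 | 0 |

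The negative sign means over-correction: the group that starts worse appears to improve more, by regression to the mean. At d = 0.25 SD the change shifts are −0.175, −0.125 and −0.075 SD.

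**Step 4: a group main effect averaged over T0 to T4.** Two of the five visits precede treatment. An effect that is constant over T2 to T4 is therefore reduced to 3/5 of its size. The imbalance is also carried. If all visits are equally correlated, the shift is d(1 + 4r)/5, which for d = 0.49 is 0.49 × 0.44 = 0.22, 0.49 × 0.60 = 0.29 and 0.49 × 0.76 = 0.37 SD.

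**Step 5: power at 0.711 SD, 32 per arm (noncentral t).** The effect is divided by √(2 − 2r) for the change contrast and by √(1 − r²) with T1 adjustment.

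| | r = 0.3 | r = 0.5 | r = 0.7 |
|---|---|---|---|
| Standardized effect, change | 0.601 | 0.711 | 0.918 |
| Power, change | 66% | 80% | 95% |
| Standardized effect, T1-adjusted | 0.745 | 0.821 | 0.996 |
| Power, T1-adjusted | 84% | 90% | 98% |

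**The case against.** A reader might infer that imbalance enters the treatment contrast uncorrected because it has passed the baseline test. The article does not support this. It ties no decision to the tests, so removing them would leave the treatment contrast as it is. Nor is the test the only place where baseline enters: T0 and T1 are levels of the planned model, and a group-by-time term does remove the baseline difference, although too strongly when r is below 1.

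A reader might also infer an inflated false-positive rate. That does not hold either. Under proper randomization the type I error over all trials stays at its nominal level, and any distortion is conditional on the imbalance that occurred. The 0.49 SD case lies at the edge of what passes; smaller imbalances give proportionately smaller shifts. Bias or power figures for an unadjusted t-test at T4 alone would describe an analysis that the article does not plan. Miss rates for a true baseline difference describe nothing here, because randomized groups have no such population difference.

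Finally, this is a condensed article, and the choice of covariates and of the model term is commonly left to the full plan. That objection stands for the mere absence of a covariate. It does not cover what the article fixes in words: a test for equality, and a treatment comparison whose repeated factor runs from T0 to T4.

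**Conclusion.** The point holds in two parts. The baseline significance tests cannot establish equality: with 32 per arm they pass observed differences of up to 0.50 SD, and they give no guidance on adjustment. Separately, the stated repeated measures model makes less efficient use of the randomization score than adjustment would, whichever term is taken as the treatment contrast.

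The loss is conditional bias and precision, not a systematic error. Its size depends on a correlation and an effect size that the article does not give. Over r = 0.3 to 0.7, T1 adjustment gains about 18, 10 and 3 percentage points of power over a change contrast (84 − 66, 90 − 80, 98 − 95). This is an improvement that should be made; it does not invalidate the trial. If the full analysis plan already adjusts for T1 and drops T0 and T1 from the repeated factor, only the wording on baseline tests needs correction.

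**What to change.** Replace the baseline tests with descriptive summaries per group (mean and SD, or number and percentage), with standardized differences if wanted. Draw no conclusion of equality from p > 0.05.

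Rewrite the model statement so that the SDQ at T2, T3 and T4 are the repeated outcomes and the T1 SDQ score is a prespecified covariate, whatever imbalance is observed. Take T0 and T1 out of the repeated factor; adding T1 as a covariate while it remains an outcome level would be incoherent. Name the group contrast at 12 months as the reported effect.

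Do the same for each secondary outcome with a T1 value. Where only T1 and T4 are measured, as with the physical assessment for the Constant score, use a single analysis of covariance at T4.

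The cost is one degree of freedom for the covariate and a small rewrite of the Statistical analyses section. No new SDQ data are needed, because the SDQ is already collected at T1.

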**Methods/Design:**

The effectiveness of an arthroscopic subacromial decompression versus usual medical care will be evaluated in a randomized controlled trial (RCT). Patients are eligible for inclusion when experiencing a recurrence of SIS within one year after a first episode of SIS which was successfully treated with a subacromial corticosteroid injection. After inclusion they will receive injection treatment again by their general practitioner. When, after this treatment, there is a second recurrence within a year post-injection, the participants will be randomized to either an arthroscopic subacromial decompression (intervention group) or continuation of usual medical care (control group). The latter will be performed by a general practitioner according to the Dutch National Guidelines for Shoulder Problems. At inclusion, at randomization and three, six and 12 months post-randomization an outcome assessment will take place. The primary outcome measure is the patient-reported Shoulder Disability Questionnaire. The secondary outcome measures include both disease-specific and generic measures, and an economic evaluation. Treatment effects will be compared for all measurement points by using a GLM repeated measures analyses.

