#### Selection of participants

Subjects participating in the study are recruited by the general practitioners involved. They introduce the study to patients who seem eligible and give interested patients a brochure about the trial, to be read at home. After having received consent, the general practitioners fax the name and telephone numbers of the interested patients to the research team. Subsequently the researcher calls the interested patients within one week. During this conversation the aim and implications of the study are explained again and the eligibility criteria are checked. Patients are eligible for participation when they meet the inclusion and exclusion criteria presented in Table 1.

If patients meet these criteria and wish to join the study, an informed consent form is signed before participation begins. The new participants receive another subacromial corticosteroid injection from the general practitioner for treatment of their first recurrence. If ineffective, this injection will be repeated within one month. Participants who have a recurrence of problems within one year after the last injection will contact their general practitioner, who will inform the researcher by fax. Subsequently the participant will be invited to visit the researcher at UMCG for a physical outcome measurement and to be randomized to one of the two treatment groups. Participants who do not have a recurrence within one year will not be randomized.

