### Outcome assessment

At inclusion (T_0_), at randomization (T_1_) and at three (T_2_), six (T_3_) and 12 months (T_4_) post-randomization, outcome assessment will take place in both study groups (Table 2). At all measurement points, outcome will be assessed by means of questionnaires which are sent to the participants by mail three days earlier. At T_1 _and T_4 _the participants are asked to visit the researcher at UMCG for an additional physical assessment. The questionnaires addressing those measurement moments can be filled in at home and be handed in at the patient's visit. The researcher checks all questionnaires for missing or incorrect data.

The outcome measures used focus on shoulder function, pain and health-related quality of life. They are disease-specific or generic, and from a patient- or physician-based perspective. The following applied measures are disease-specific and patient-based: the Shoulder Disability Questionnaire, the Shoulder Pain Score and the Shoulder Rating Questionnaire. The Individual Relative Constant Score is a disease-specific as well as a patient- and physician-based instrument. The Short-form 36 Health Survey and the Patient-perceived recovery are both generic and patient-based. For the cost effectiveness analysis a generic, patient-based questionnaire will be used. The specific characteristics of the outcome measures will be mentioned below.

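### The repeated-measures comparison runs over T0 to T4, which includes two scores taken before allocated treatment, while the trial is sized on the difference at T4

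*Protocol article*

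**What the plan says.** The Statistical analyses section of the protocol article gives one comparative analysis of effectiveness: "To compare treatment effects from measurement points T_0 _to T_4_, a GLM repeated measures analyses will be performed". The abstract has the same scope: "Treatment effects will be compared for all measurement points by using a GLM repeated measures analyses".

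The Outcome assessment section defines the five points: "At inclusion (T_0_), at randomization (T_1_) and at three (T_2_), six (T_3_) and 12 months (T_4_) post-randomization". Selection of participants shows what separates the first two from the rest:

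- After inclusion, everyone gets the same treatment: "The new participants receive another subacromial corticosteroid injection from the general practitioner for treatment of their first recurrence".
- Only at a second recurrence is the participant "invited to visit the researcher at UMCG for a physical outcome measurement and to be randomized to one of the two treatment groups".

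The Sample size section is written for one time point. It speaks of a "clinically relevant difference in shoulder function (35% differences in means) one year after randomization between the intervention and control group" and assumes that "one year after randomization 50% of the participants will have recovered with conservative treatment", against 85% with surgery.

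**The concern.** Allocated treatment cannot have acted at T0 or T1, so the expected group difference is zero at both. They nevertheless sit among the five repeated levels over which treatment effects are to be compared.

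A repeated-measures GLM on those levels offers two standard tests that involve group, and neither is the contrast behind the sample size. The main effect averages two expected zeros with three post-randomization differences. The interaction asks whether the group difference is the same at all five points. A difference at T2 or T3 alone could make it significant, and it yields no 12-month estimate.

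T0 is also awkward as a level of a time factor. Randomization follows whenever the second recurrence occurs within a year of the last injection, so the T0–T1 interval varies between participants.

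At stake is the main conclusion of a trial that its Discussion links to guideline updates. A real 12-month benefit could be missed through a diluted term, or success could be declared without evidence at 12 months.

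**Working it through.** **Inputs from the article.** T0 and T1 precede allocated treatment. T2, T3 and T4 are at 3, 6 and 12 months. There are 32 per arm, two-sided alpha is 5% and power is 80%.

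**Assumptions.** The article gives no SD, correlation or effect profile. I take equal variances, no missing data, and correlation ρ = 0.3, 0.5 or 0.7, either equal between all visits (compound symmetry) or AR(1) with visits treated as equally spaced.

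**1. The plan's own figure.** For 50% against 85%, the uncorrected size per arm is [1.96·√(2·0.675·0.325) + 0.842·√(0.5·0.5 + 0.85·0.15)]² / 0.35² = 26.9, so 27. The continuity correction gives (26.9/4)·[1 + √(1 + 4/(26.9·0.35))]² = 32.4, so 33. The stated 32 is within one per arm. The trial is thus sized on a comparison at T4 alone.

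**2. Effect size.** A t-test with 32 per arm has 80% power at 0.71 SD (normal approximation: 2.80/√(32/2) = 0.70). I use 0.71 SD as the true T4 difference.

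**3. Group main effect over T0–T4.** Share of the T4 effect recovered:

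- Full effect at T2, T3 and T4: (0+0+1+1+1)/5 = 60%.
- Effect building by thirds: (0+0+1/3+2/3+1)/5 = 40%.
- Effect at T4 only: 1/5 = 20%.

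These shares do not depend on correlation. The 60% is a ceiling as long as the effect at T2 and T3 is no larger than at T4.

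Under compound symmetry the five-visit mean has variance (1+4ρ)/5, which is 0.44, 0.60 and 0.76. The noncentrality is share × 0.7115 / √(2/32 × variance), on 62 df. At ρ = 0.5:

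- Gradual effect: 0.2846/0.1936 = 1.47, power 30%.
- Full effect: 0.4269/0.1936 = 2.20, power 58%.

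**4. Group-by-time interaction.** This is the multivariate test on 4 and 59 df. Under compound symmetry the noncentrality is (32/2) × Σ(δt − mean δ)² / (1−ρ). For the gradual effect at ρ = 0.5: 16 × 0.506 × 0.7556 / 0.5 = 12.2, power 78%.

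**5. T4 difference adjusted for T1.** The variance factor is 1 − r², where r is the T1–T4 correlation (ρ under compound symmetry, ρ³ under AR(1)). At ρ = 0.5:

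- Compound symmetry: 0.7115/√(0.0625 × 0.75) = 3.29, power 90%.
- AR(1), r = 0.125: noncentrality 2.87, power 81%.

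**6. T4 minus the mean of T0 and T1**, a contrast available inside the stated model. Its variance factor is 1.5(1−ρ) under compound symmetry (1.05, 0.75, 0.45) and 1 + (1+ρ)/2 − ρ³ − ρ⁴ under AR(1) (1.61, 1.56, 1.27).

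**Power at ρ = 0.3 / 0.5 / 0.7**

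| Test | Compound symmetry | AR(1) |
|---|---|---|
| Main effect, full effect | 72 / 58 / 49% | 84 / 71 / 57% |
| Main effect, gradual | 39 / 30 / 25% | 51 / 39 / 30% |
| Interaction, full effect | 83 / 94 / 99.7% | 62 / 68 / 85% |
| Interaction, gradual | 61 / 78 / 95% | 38 / 38 / 47% |
| T4 minus mean of T0 and T1 | 78 / 90 / 99% | 60 / 61 / 70% |
| T4 unadjusted | 80% | 80% |
| T4 adjusted for T1 | 83 / 90 / 97% | 80 / 81 / 85% |

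If the effect appears at T4 only, main-effect power drops to 10–17% over the same correlations.

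**The case against.** The article does not say which term carries the treatment effect. With baseline inside the time factor, group-by-time is the natural term to read. T0 and T1 then serve as the reference for change, and the dilution figures do not apply. This stands. A reader might infer that the trial's estimate will be biased towards zero and the trial underpowered, but the text does not support that as an unconditional statement.

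Nor is baseline information necessarily lost. Within-patient terms remove stable differences between patients, which is why interaction power rises with correlation. A contrast of T4 against the mean of T0 and T1 is open to the same model and matches T1 adjustment under compound symmetry at ρ = 0.5. This stands too, although under AR(1) that contrast falls to 60–70% while T1 adjustment keeps 80–85%.

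A condensed article may also leave the named contrast and the covariates to an analysis plan that is not shown. Their absence is therefore not the finding. The T0–T4 span is different, because it is stated, and naming a contrast later would not take the two earlier scores out of the outcome set.

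Finally, the Discussion asks whether improvement comes sooner as well as more fully, so a test over time is relevant to the aim. That is fair, but the T2 and T3 differences answer it, and T0 is not needed for that.

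**Conclusion.** The stated analysis span does not match the contrast on which the trial was sized. That much rests on the text alone.

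The consequences are conditional. If the main effect is read as the treatment effect, it is diluted to at most 60% of the T4 effect (40% for a gradual build-up), with power of about 25–72% under compound symmetry or 30–84% under AR(1) for the full and gradual profiles. If the interaction is read, the 12-month difference is neither estimated nor singled out, and power lies anywhere from about 38% to over 99%. A certain loss of power cannot be claimed.

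All power figures assume a 0.71 SD difference at T4, 32 evaluable per arm and correlations of 0.3 to 0.7. The sample size itself is not in question here. The case for change is that the T1-adjusted T4 contrast holds at least 80% power in every scenario checked and answers the question the trial was sized for.

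**What to change.** Replace the T0–T4 comparison with a model that takes SDQ at T2, T3 and T4 as outcomes and SDQ at T1 as covariate, with group, time and group-by-time.

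- Name the adjusted between-group difference at T4, with its 95% CI, as the single primary contrast.
- Make the T2 and T3 differences secondary. They address whether improvement comes sooner.
- Use T0 descriptively or as an additional covariate.
- Keep T1 in the model whatever the baseline comparison tests show.
- Bring the abstract's wording into line.

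The cost is a change of wording before analysis. N, visits and questionnaires stay as they are, because SDQ is already collected at all five points.

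### GLM repeated measures over T0 to T4 defaults to complete cases, which defeats the intention-to-treat aim unless missing values are imputed first

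*Protocol article*

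**What the plan says.** The Statistical analyses section of the protocol article fixes the software (SPSS 12.0), the span (T0 to T4) and the method: "a GLM repeated measures analyses will be performed". The next sentence gives the analysis principles: "Data will be analyzed according to the intention-to-treat principle and the per-protocol principle". The Abstract also names GLM repeated measures for all measurement points.

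The Outcome assessment section sets the five points: T0 at inclusion, T1 at randomisation, and T2, T3 and T4 at three, six and 12 months after randomisation. On collection it says: "At all measurement points, outcome will be assessed by means of questionnaires which are sent to the participants by mail three days earlier". Only T1 and T4 include a visit, at which the form can be handed in. The researcher checks all questionnaires for missing or incorrect data.

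The Sample size section targets the difference one year after randomisation and needs 64 participants, 32 per group. It then adds the allowance: "When a dropout rate of 10% is taken into account, 70 participants are to be included".

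The article does not say how a participant with a missed assessment is handled, and it gives no expected rate of missed forms.

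**The concern.** GLM repeated measures in SPSS takes one row per participant and, by default, drops any row with a missing value among the repeated measures. Run as named, it analyses only participants with all five SDQ scores. Three things follow.

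- **Known outcomes are discarded.** A participant with a 12-month SDQ is lost for a missed T2 or T3 form, or for a missed T0 form completed before the second course of injection and before randomisation. A participant who drops out after T3 loses the T2 and T3 data already collected.
- **A stronger assumption is needed.** A complete-case comparison is valid only if being complete is unrelated to outcome within each arm. Surgery is compared with general practitioner care on a patient-reported outcome, and no blinding is described, so non-return could plausibly depend on arm and on recovery. A likelihood-based mixed model needs only that missingness depends on observed data.
- **The sample size allowance does not cover it.** The 10% is described as dropout, and nothing is added for isolated missed forms.

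**Working it through.** **Inputs from the article.** Two-sided 5% level and 80% power; 64 evaluable (32 per group); 10% dropout; 70 included; five assessments in the model, three of them after randomisation.

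**The plan's own figure.** The Sample size section assumes that "one year after randomization 50% of the participants will have recovered with conservative treatment" and that "85% will successfully recover by means of arthroscopic subacromial decompression". For 50% against 85%, the pooled two-proportion formula gives 26.9, so 27 per group. With continuity correction it gives 32.4 per group, rounded up to 33 (66 in total), within two participants of the stated 64. No SD is given, so the difference-in-means reading cannot be checked directly. Solving back from 32 per group:

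d = (1.960 + 0.842) × √(2/32) = 0.70 SD (0.71 with the t distribution).

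This value is used below only to put a scale on the loss.

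**The dropout allowance.**
- 70 × 0.90 = 63, one short of 64. Power at d = 0.70 is 0.794.
- That single-person gap comes from rounding the inflation (64/0.90 = 71.1, so 72), not from GLM.
- Up to 70 − 64 = 6 participants (8.6%) can be incomplete before the number falls below 64.

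**Adding missed forms.** The missed-form rate m is an assumption. It is taken as independent across forms, with all 70 randomised. Complete cases = 70 × (1 − m)^k, where k is the number of forms that can be missed. Power is for a two-sample comparison at d = 0.70, normal approximation.

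| m | k = 5: complete | power | k = 3 (T2–T4): complete | power |
|---|---|---|---|---|
| 3% | 70 × 0.859 = 60.1 | 0.775 | 70 × 0.913 = 63.9 | 0.799 |
| 5% | 70 × 0.774 = 54.2 | 0.732 | 70 × 0.857 = 60.0 | 0.774 |
| 8% | 70 × 0.659 = 46.1 | 0.662 | 70 × 0.779 = 54.5 | 0.734 |

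The t-test at 0.711 SD agrees to within 0.01. If T1 alone is taken as always complete (k = 4), the numbers are about 62, 57 and 50, with power about 0.79, 0.75 and 0.70.

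**Break-even rate.** Complete cases stay at 64 or more while (1 − m)^k ≥ 64/70. That means m up to about 1.8% for k = 5, or about 2.9% for k = 3.

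**The case against.** A reader might infer that the section contradicts itself. The text does not support that. Analysis by allocated group is compatible with GLM, no complete-case population is stated, and imputation before GLM is not excluded. It could be set in a full protocol or analysis plan that is not shown. Silence on missing data is therefore no fault in itself. What stands is that the procedure actually named is one that needs such a rescue to honour intention to treat.

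A reader might also infer that the analysed number will fall below 64. That depends on a rate the article does not give: with six or fewer of 70 incomplete, it does not.

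The k = 5 column is the harsher model. T1 is collected around the randomisation visit and T4 at a visit, so both should be more complete than the mailed T2 and T3 forms. Missed forms also tend to cluster in people who drop out, for whom 10% is already allowed. Clustering leaves more complete cases than independence does at the same rate. The researcher's check helps with gaps in returned forms but not with forms never returned.

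The 0.70 SD is back-solved, and 64 is closer to a two-proportion calculation, so the power figures are illustrative. Nothing in the article shows that dropout depends on arm or outcome; the bias is a plausible risk, not a demonstrated one. All of these limits stand. They reduce the size of the point but do not remove it.

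**Conclusion.** The point holds in a limited form. Run as named, the analysis is restricted to participants with all five assessments. It discards known 12-month outcomes for a single missed form and defeats the intention-to-treat aim unless values are imputed first. The firmer grounds are the stronger missing-data assumption and the discarded data; the loss of power is secondary.

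On size, the planned 10% dropout alone leaves 63, so there is no margin for isolated gaps. With 3% to 8% of forms missing, complete cases range from about 64 down to 46 of 70, and illustrative power from about 0.80 down to 0.66, depending on which forms can be missed. These figures rest on assumed, independent missingness, on an effect size implied by 32 per group, and on all 70 being randomised. The last is generous, because the Selection of participants section does not randomise those without a second recurrence within a year.

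**What to change.** Replace GLM repeated measures for the SDQ with a likelihood-based mixed model for repeated measures. Outcomes are T2, T3 and T4; participants are analysed by allocated group; the model includes treatment, time and treatment by time, with T1 SDQ as covariate. Report the treatment contrast at T4, the time point used for the sample size. T0 then leaves the outcome vector, so a missing T0 form removes nobody, and a missed T2 or T3 form no longer costs the T4 value.

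If GLM is kept, state that multiple imputation is done first, so that all randomised participants are retained.

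The cost is analysis wording and syntax; visits, forms and data collection do not change. The mixed model still assumes data are missing at random, and a participant with no SDQ after randomisation contributes nothing to it, so the number of such participants should be reported by arm.
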